#### **ii. Missing baseline covariate data**

Participants with outcome data will not be excluded if they are missing baseline covariate data, in order to satisfy the principles of an ITT approach. Thus, for missing data in this category, mean imputation techniques will be used. Alternatively for some variables, the most recent value from the longitudinal TwinsUK cohort data will be imputed, if these is deemed to be within a sensible period of time. The timeframe will vary according to the variable in question. For example, education level is unlikely to change over a 5-year period in this age group. While mean imputation can introduce bias in statistical estimates, the randomisation at baseline ensures baseline variables are independent of which arm the participant is in. All imputation of unknowns with approximated values will be decided on before unblinding.

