| Vitamin B12 µg/d             | 3.5 (1.9)      | 4.4 (2.3)      | 3.7 (2.0)      |  | 2.9 (1.6)      | 2.6 (1.3)      | 0.026* |
| Folate µg/d                  | 222.1 (82.9)   | 212.5 (77.3)   | 220.0 (81.2)   |  | 183.8 (77.1)   | 212.8 (99.9)   | 0.079  |
| Vitamin C µg/d               | 91.4 (73.9)    | 61.9 (26.1)    | 84.9 (67.3)    |  | 69.9 (47.3)    | 72.4 (43.5)    | 0.084  |
| Vitamin D µg/d               | 3.5 (3.8)      | 2.9 (1.9)      | 3.3 (3.4)      |  | 2.7 (2.3)      | 2.1 (2.8)      | 0.200  |
| 25-Hydroxy D3 µg/d           | 0.0 (0.1)      | 0.0 (0.0)      | 0.0 (0.1)      |  | 0.4 (1.2)      | 0.0 (0.2)      | 0.092  |
| Vitamin D3 µg/d              | 0.3 (0.6)      | 0.6 (0.9)      | 0.4 (0.7)      |  | 0.3 (0.7)      | 0.3 (0.8)      | 0.228  |
| Vitamin E µg/d               | 8.0 (3.3)      | 8.9 (5.8)      | 8.2 (3.9)      |  | 6.2 (2.6)      | 8.2 (5.1)      | 0.014* |
| Vitamin K1 µg/d              | 78.3 (89.5)    | 54.7 (37.4)    | 73.1 (81.3)    |  | 50.2 (37.8)    | 49.1 (53.5)    | 0.442  |
| Food groups and other |                |                |                |  |                |                |        |
| Vegetables g/d               | 160 (120)      | 107 (63)       | 149 (112)      |  | 141 (64)       | 95 (61)        | 0.469  |
| Fruits g/d                   | 143.5 (104.2)  | 148.9 (107.7)  | 144.7 (104.0)  |  | 141.2 (141.5)  | 143.1 (92.2)   | 0.167  |
| Alcohol g/d                  | 9.7 (15.6)     | 18.6 (21.3)    | 11.6 (17.2)    |  | 7.7 (8.7)      | 13.5 (19.8)    | 0.063  |
| Water g/d                    | 1931.3 (625.8) | 2075.4 (840.2) | 1963.0 (673.4) |  | 1858.9 (622.3) | 1848.2 (782.2) | 0.124  |
| Missing Data (n)             | 10             | 3              | 13             |  | 20             | 4              | 24     |

All data presented as mean (standard deviation). Please note the nutritional intake from the intervention sachet is not included in these dietary data. NSP: non-starch polysaccharides. AOAC fibre comprises of the total amount of non-digestible polysaccharides, and includes e.g., lignin and resistant starches, measured with a set of methods developed by the Association of Analytical Chemists (AOAC). \* Denotes significance.

P values are within group comparisons of the total population between baseline and end of intervention performed using a two-sided paired t-test

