## 4. Trial Population

### ***a. Screening data and eligibility criteria***

Participants will be recruited from the TwinsUK databases and invited to attend a virtual visit using video teleconferencing. A subset will later be invited to the department in St Thomas' Hospital to repeat the physical performance measures. Those who are aged 60 years or older and who have a dietary protein intake of <1.3g/kg/day on their most recent food frequency questionnaire will be contacted and invited for screening.

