### ***d. Overall Improvement***

In addition to analysing the primary and secondary outcomes by arm, group-wide comparisons will be carried out for the following variables of interest: weight, BMI, SPPB

score, balance score, grip strength, chair rise time, gait speed, IPAQ MET minutes/week, IPAQ score, SNAQ score, CANTAB cognitive test results and serum metabolites.

Paired tests will be carried out to assess for differences between baseline and study end point, two sample t-tests for continuous variables (normally distributed), Mann-Whitney test for non-normally distributed continuous variables, and Pearson's chi-squared tests for categorical variables.

While there is no control group for these analyses, these will tell us whether the protein and exercise intervention that all twins will receive was beneficial for the aforementioned variables of interest, irrespective of gut microbiome modulation with a prebiotic food supplement. This analysis will also be repeated using two subgroups of interest, protein intake at baseline, and frailty index at baseline.

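### SAP 7.5.2 justifies filled baseline covariates by randomisation, which covers arm-comparison models but not subgroup placement, microbiota–strength models or before-after tables

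*Combined protocol and SAP*

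**What the plan says.** SAP 7.5.2 (Missing baseline covariate data) opens with the aim of keeping people in the intention-to-treat analysis: "Participants with outcome data will not be excluded if they are missing baseline covariate data". For these gaps "mean imputation techniques will be used"; alternatively, for some variables, "the most recent value from the longitudinal TwinsUK cohort data will be imputed", if it is recent enough, with the time limit varying by variable. The section then concedes a weakness, "While mean imputation can introduce bias in statistical estimates", and meets it with a single argument: "the randomisation at baseline ensures baseline variables are independent of which arm the participant is in".

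No sentence restricts the filled values to models that compare the arms. Baseline values have other uses in the SAP:

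- Section 5.3 forms subgroups by baseline protein intake, IPAQ MET minutes, frailty index, SPPB and microbiome diversity, among others.
- Section 5.4 plans group-wide before-after tests with no control group, and adds: "This analysis will also be repeated using two subgroups of interest, protein intake at baseline, and frailty index at baseline".
- Section 7.1 (Food diary data) compares baseline and end diaries with paired tests.
- Section 7.2.2.1 relates microbiota dissimilarity to differences in muscle strength, with diet (HEI), BMI and frailty index as covariates.

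**The concern.** Randomisation makes a baseline variable independent of arm. It does not make it independent of the outcome, of a microbiota feature or of the same variable measured later. The argument in 7.5.2 therefore carries over to none of the other uses:

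- **Subgroup placement.** A person given the overall mean of baseline protein is assigned to a subgroup by the imputation rule, not by a measurement. That blurs who is in each subgroup, any contrast between subgroups, and the uncontrolled before-after tests run within them.
- **Association models.** Replacing a confounder by its mean in some people leaves their part of the confounding unadjusted. Arm allocation plays no role in removing it.
- **Before-after comparisons.** A filled baseline set against a measured end value can produce a change that comes from the filling. The one cohort source of protein intake that the SAP names is the value "on their most recent food frequency questionnaire" used for screening, whereas the end value comes from a 3-day food diary. If cohort values were used, a change of instrument would be mixed with a change of diet.

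At stake are secondary and exploratory results, including the reported fall in energy intake.

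**Working it through.** **1. The argument where it applies.** In a simulation of 36 twin pairs (4,000 runs, mean-filled covariate, 13/72 or 22/72 missing, either at random or more often at low values), the estimated arm effect had bias of about 0 and was rejected in 4.9–5.3% of runs against a nominal 5%. The SAP's reasoning is correct for that use.

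**2. Numbers available in Table S4.** The headings give 56 women and 16 men (72). The missing-data row gives 10 women and 3 men at baseline, so 46/13 (59) observed. At study end it gives 20 and 4, so 36/12 (48) observed.

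**3. Which n reproduces the printed totals?** From the sex-specific values, M = (n₁m₁ + n₂m₂)/N and SD = √{[Σ(nᵢ−1)sᵢ² + Σnᵢ(mᵢ−M)²]/(N−1)}.

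Baseline energy, with 1504.4 (347.6) in women and 1797.5 (484.0) in men:
- 56/16: (56×1504.4 + 16×1797.5)/72 = 113,006.4/72 = 1569.53, SD 397.68. Printed: 1569.5 (397.7).
- 46/13: (46×1504.4 + 13×1797.5)/59 = 92,569.9/59 = 1568.98, SD 396.51.

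Rounding of the inputs moves the second mean by at most 0.05, to 1569.03, and the printed value cannot lie below 1569.45. Among all splits of 40–56 women and 8–16 men, only 56/16 matches both mean and SD. The 46/13 line only tests the weights. It reuses the printed sex means, so it is not an estimate of the diary-only mean, which is unknown.

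| Table S4 row | Printed | 56/16 | 46/13 | 36/12 |
|---|---|---|---|---|
| Baseline energy | 1569.5 (397.7) | 1569.53 (397.68) | 1568.98 (396.51) | – |
| Baseline sodium | 1853.4 (794.0) | 1854.48 (795.28) | 1853.37 (794.06) | – |
| Baseline potassium | 2447.2 (691.5) | 2447.71 (693.60) | 2447.17 (691.50) | – |
| Baseline calcium | 732.2 (274.2) | 732.59 (274.71) | 732.18 (274.22) | – |
| End energy | 1476.0 (438.7) | 1468.78 (434.69) | – | 1476.05 (438.71) |

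Sodium, potassium and calcium fit the 59 baseline diaries and not 72. End energy fits the 48 end diaries. Protein and fat cannot tell 72 from 59 (means 60.27 v 60.25 and 66.09 v 66.06).

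**4. Other tables.** Baseline energy pools to the same 72-person value in Table S6 (36/36: 1569.55, SD 397.67) and in Table S3 (22/50: 1569.50, SD 397.64; 46/26: 1569.51, SD 397.65). In Table S5 it fits the full 54/15 in the headings (1592.60, SD 386.17; printed 1592.6 (386.2)), although that table lists 14 as missing; the remaining 43/12 would give 1592.83 (385.39).

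**5. How many pairs could be affected.** With 59 baseline and 48 end diaries among 72 people, the number with both lies between 59 + 48 − 72 = 35 and 48. People with an end diary but no baseline diary therefore number between 48 − 48 = 0 and 48 − 35 = 13. A baseline value from outside the diaries could sit in 0 to 13 of at most 48 paired differences (0–27%).

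**The case against.** The strongest reply concerns scope. Section 7.5.2 is about covariates, is motivated by intention to treat, and covers people who would otherwise drop out of a model. A before-after baseline is not a covariate, so on a strict reading it was never included. Most of Table S4 agrees: the rows that can be tested fit the 59 diaries, apart from energy. One deviant row might be a wrong column or a different energy source, and the documents do not say which. This stands as a reading of the rule. It does not explain the energy row, and it does not reach the association models, whose HEI, BMI and frailty index are covariates in the plain sense, or subgroup membership, which no missing-data text addresses.

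The SAP also has safeguards. The per-protocol population is complete-case (section 5), complete-case sensitivity analyses are planned (7.5.1), imputation is decided before unblinding (7.5.2), and subgroups are acknowledged as unpowered (5.3). These help the arm comparison. None says how a missing baseline value is treated in the non-randomised uses.

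A reader might infer that the fall in energy intake is an artefact. The documents do not support that. The paired test may contain no filled value at all (step 5), and fat falls in the same way (p=0.032 overall; 0.01 prebiotic, 0.60 placebo). Fat also looks unfilled. Its baseline arm p-value of 0.11 in Table S6 matches an unpaired test on 30/29 people (difference 8.9, SE 5.53, p=0.11) and not 36/36 (SE 5.01, p=0.08). The 30/29 split and the unpaired test are assumptions.

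A reader might also want a figure for residual confounding or misplaced subgroup members. The 18% (13/72) is diary missingness and the 31% (22/72) is CANTAB missingness. No missing rate is given for HEI, BMI or frailty index, the first and last of which come from cohort data for everyone by design (SAP 4.2), and no subgroup cut-points are stated.

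**Conclusion.** The concern holds in limited form. The justification in 7.5.2 covers adjustment covariates in arm-comparison models and nothing further. It should not carry filled values into the microbiota–strength models or into subgroup placement. The tables also suggest, without proving, that 13 of 72 baseline energy values (18%) came from somewhere other than the diaries counted in the same table.

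A reader might infer that the trial's main result is affected. It is not: the primary arm comparison is not biased by this, and an arm contrast within a subgroup remains a randomised comparison even if membership rests on filled values. Whether the values were means, cohort values or something else, and whether they entered the paired p-values, cannot be settled from the documents. The only size they support is 0 to 13 of at most 48 pairs. This rests on the missing-data row applying to every diary variable and on the printed sex-specific values being correct to the decimal shown.

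**What to change.** 1. State in SAP 7.5.2 that filled values are used only as adjustment covariates in models that compare the randomised arms.
2. Use observed values only for subgroup membership and for the baseline side of before-after comparisons.
3. For covariates in the association models, use observed values or multiple imputation.
4. Print n for each row of the before-after and subgroup tables.
5. Check the source of baseline energy in Supplementary Tables S3–S6. Recompute it from the diaries in S4–S6, and rerun its paired tests on people with both diaries (between 35 and 48).

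The cost is a few sentences and the rerun of one row in three tables. The downside is fewer people in those secondary analyses: for a subgroup based on diary protein, 59 instead of 72. The paired energy test loses at most 13 people, because end diaries already cap it at 48.

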***e. Planned tables and figures***

**i. Table 2: Planned tables and figures**

| Table/Figure | Title                                                     |
|---------------------|------------------------------------------------------------------|
| Figure 1            | Participant Flow Diagram (see 4.3)                               |
| Table 1             | Comparison of participants to those who declined/were ineligible |
| Table 2             | Baseline Characteristics, by study arm (see 4.2.1)               |
| Table 3             | Group wide comparisons between baseline and study end point      |
| Table 4             | Dietary Intakes at baseline and study end                        |
| Table 5             | Cognition Factor Analysis                                        |
| Table 6             | Adverse events, dropouts, compliance                             |
| Table 7             | Linear Mixed models for primary and secondary outcomes           |
| Table 8             | Sensitivity Analyses                                             |
| Table 9             | Subgroup Analyses                                                |
| Table 10            | Validation Analyses                                              |

